### Objectives

#### Primary objective – effects of treatment on drinking behavior

This study examines the efficacy and effectiveness of EMDR + TAU versus TAU only on drinking behaviour in a sample of alcohol dependent participants.

We operationalize drinking behavior as: a) changes in number of heavy drinking days (days on which ≥ 5 standard drinks of alcohol are consumed); b) time to first alcohol drink (only relevant if abstinence was reached before the previous assessment); c) changes in total drinks consumed in the past 30 days; and d) changes in average drinks per occasion in the past 30 days (total drinks divided by drinking days). Participant-reported information is backed-up with changes in relevant biomarker data (derived from blood samples at all time-points): carbohydrate-deficient transferrin (CDT) combined with serum γ-glutamyltransferase (GGT). An overview of the measurements at different time points is given in Table 1.

**Table 1 Tab1:** **Measurements of primary, secondary and tertiary objectives: drinking behavior, mediators, moderators and predictors and quality of life**

	Outcome	Measurement	Baseline screening	T0	T1	T2	T3
		-interview (i)		Pretreatment	Posttreatment	1 month FU	6 months FU
		-self-report (s)					
		-reaction time (r)					
		-bloodsample (b)					
1	Recent and lifetime use, indications for psychiatric or medical evaluation, addiction treatment history and current abuse or dependence (DSM-IV)	MATE (part 1–4) (i)	X				
2	Comorbid psychiatry (DSM-IV)	MINI-plus (i)	X				
3	Motivation to change	RCQ-D (s)		X			
4	Harmful alc. use	AUDIT (30 d) (s)		X	X	X	X
5	Self-efficacy	SELD (s)		X	X	X	X
6	Health outcome	EQ-5D (s)		X	X	X	X
7	Quality of life	CRA-HS (s)		X	X	X	X
8	Alcohol craving	PACS (s)		X	X	X	X
9	Desire thinking	DTQ (s)		X	X	X	X
10	Pos. and neg. affect	PANAS-SF (s)		X	X	X	X
11	Rumination	PTQ (s)		X	X	X	X
12	Drinking behavior	TLFB (30 d) (i)		X	X	X	X
13	Alcohol attentional bias	Alcohol Stroop (r)		X	X	X	X
14	Alcohol implicit assoc.	Valence IAT (r)		X	X	X	X
15	Biomarkers chron. alc. use	GGT + CDT (b)		X	X	X	X

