## Methods/design

### Design

This study is a randomized controlled trial with two arms: EMDR + TAU versus TAU. The two groups are compared pre-treatment (T0), post treatment (T1 = T0 + 8 weeks) and at follow up one (T2) and six months (T3) post treatment, on variables linked to the research questions. This amounts to a 2 × 4 design with the between factor condition (EMDR + TAU vs. TAU) and within factor time (pre- x post intervention × 1 × 6 months follow-up).

Both groups will be assessed at the same time-points, whereby a substantial part of both groups may still receive TAU at follow-up after 1 month, but may no longer receive TAU at follow-up after 6 months.

The current study is hybrid in that it tries to broaden the generalizability of the outcomes by recruiting a representative, but complex sample while maintaining some of the rigor of efficacy research (e.g. using training and supervision, monitoring of and feedback on treatment fidelity). This allows to analyze data from an effectiveness (outcome in real life circumstances, using all data, including imputed data in case of study drop-out etc.) and an efficacy (outcome under ideal circumstances using only completers data) viewpoint.

The design of this study was approved by the Medical Ethics Committee of Medisch Spectrum Twente and is registered as study NL43892.044.13.

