### Power and sample size calculation

Since two active treatment arms are compared and the sample is expected to be relatively heterogeneous regarding baseline variables such as dependence severity, drinking status and other substance use, it is estimated that the effect size will be relatively small. Clinical relevant differences on the primary outcome variable (changes in number of heavy drinking days in the previous 30 days) were calculated on the basis of data of a recent study [46]. In patients with an alcohol-use disorder referred to in- or outpatient alcohol treatment the mean baseline score for heavy drinking days (≥5 drinks in a single day, over the past 30 days) was 16.33 (SD 11.99). Treatment outcome was such that undertreated patients (<75% attendance of the number of sessions recommended by treatment allocation guidelines, n = 618) showed a reduction of 8.7 heavy drinking days (±12.5) while overtreated patients (>110% attendance of sessions recommended) showed a reduction of 12.5 heavy drinking days (±12.2, n = 362). The difference between under- and overtreated patients is at least 3.8 heavy drinking days over the past 30 days which corresponds to an effect size of *d* = 0.31 or *f* = 0.15).

Subsequent poweranalysis in G*Power version 3.1.2. [47] (ANOVA: repeated measures, within-between interaction) indicated a sample size of 74 to demonstrate this effect (keeping α at 0.05 and power at 0.80 and using 2 groups and 3 measurements (concerning changes in the number of heavy drinking days between 4 time points)). Attrition is estimated to be relatively high at 33%. Therefore we add 26 participants (100 patients in total, 50 in each treatment arm), to meet the required sample size.

To minimize missing values RA1 will use email, text messages, telephone calls, and/or contacts with participants’ regular therapists to remind participants about their assessment appointments. All participants will receive financial compensation of 25 euros (in the form of a gift cheque) for every complete assessment at T2 and T3, regardless of whether or not the participant drops out of treatment.

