### Termination of treatment

Regarding EMDR treatment, completers are defined as completing five or more of the scheduled seven EMDR sessions, allowing for some flexibility on the basis of clinical need. Those who attend four EMDR sessions or fewer for any reason comprise a premature termination of treatment (PTT) group.

Regarding TAU, a similar distinction is made whereby a completer attended five or more weeks of treatment (at least one face-to-face contact weekly) between T0 and T1 while those who attend four weeks or less of TAU fall in the PTT category.

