### Analyses

All analyses will be executed using SPSS. Summary tables will be provided for all baseline, end of treatment and follow-up variables. Data will be summarised using frequency tables (with confidence intervals when applicable), and descriptive statistics (mean, median, interquartile range, number and percentages of participants and two-sided, 95% confidence intervals when appropriate).

Changes in the number of heavy drinking days in the past 30 days will be used to analyze the efficacy and effectiveness of EMDR. Since this primary outcome variable is continuous, a repeated measures ANOVA will be carried out with 2 group (EMDR + TAU versus TAU) and 4 time (pre-, post-treatment, 1 and 6 month follow-up) factors. Randomization stratum will be used as a covariate. Effect sizes will be calculated.

All allocated participants will be included in the primary analysis (intention-to-treat, ITT). Since an ideal ITT requires a complete set of data [89], multiple imputation (or a similar strategy) will be used for missing data, if possible. In addition a per-protocol (PP or completers) analysis will be done. ITT analyses will provide insight into the effectiveness of the treatment in real life whereas PP analysis gives insight into the efficacy or the ability for the treatment to reach its intended effect under ideal circumstances.

Repeated measures of continuous secondary variables such as time to first alcohol consumption, number of total drinks consumed and average drinks per occasion in the past 30 days, severity of the dependence, level of rumination, negative affect, desire thinking, craving, coping self-efficacy, quality of life, biomarkers will be analyzed by carrying out a repeated measures ANOVA with 2 group (EMDR + TAU versus TAU) and 3 (post treatment versus 1 versus 6 month follow-up: time to first drink variable derived from TLFB data) or 4 time (pre- versus post-treatment versus 1 versus 6 month follow-up: all other data) factors.

Distribution of premature treatment termination (PTT), a categorical variable, will be analysed using chi-square tests. A range of baseline clinical characteristics potentially associated with subsequent PTT will be examined. A logistic regression analysis will be conducted to examine the relative contribution of key variables to PTT status. A Kaplan–Meier survival curve will be used to illustrate the distribution of PTT prior to the completion threshold at session 5.

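### The completers analysis is said to show efficacy, but the two completer sets are formed after randomisation by different rules and are not a randomised comparison

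*Protocol article*

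**What the plan says.** The primary objective has two parts: "This study examines the efficacy and effectiveness of EMDR + TAU versus TAU only on drinking behaviour". The Design section ties the first part to an "efficacy (outcome under ideal circumstances using only completers data) viewpoint".

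The Analyses section makes intention-to-treat primary: "All allocated participants will be included in the primary analysis (intention-to-treat, ITT"). It then adds that "In addition a per-protocol (PP or completers) analysis will be done". It assigns effectiveness to the first analysis and efficacy to the second, stating that "PP analysis gives insight into the efficacy or the ability for the treatment to reach its intended effect under ideal circumstances".

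The Termination of treatment section defines the groups. For EMDR, "completers are defined as completing five or more of the scheduled seven EMDR sessions", and "Those who attend four EMDR sessions or fewer for any reason comprise a premature termination of treatment (PTT) group". For TAU, a completer has weekly face-to-face contact in at least five weeks between T0 and T1. The article does not say whether patients in the EMDR + TAU arm must meet both rules.

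The Power and sample size section reports, from another study, reductions of 8.7 heavy drinking days in low attenders and 12.5 in high attenders: "The difference between under- and overtreated patients is at least 3.8 heavy drinking days over the past 30 days". That gap is also the effect for which the trial is sized.

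**The concern.** Whether a patient completes is known only after randomisation and can depend on how that patient is doing. An EMDR completer has kept up with at least five sessions of an added treatment. A TAU completer has only stayed in usual care, and nobody can tell which TAU patients would also have stayed in EMDR. Restricting both arms to completers therefore compares two differently selected groups. This would be so even with one common yardstick, and the protocol uses two.

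The protocol itself expects completers to differ from the rest, since it plans to model premature termination on baseline characteristics. Nothing planned repairs the contrast. Randomisation stratum is the only fixed covariate, and the others may be added after correlations have been inspected.

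At stake is what the report may say about one named part of the primary objective: a difference between self-selected groups could be presented as what EMDR achieves when it is received.

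**Working it through.** **Inputs from the protocol (Power and sample size).** Reductions 8.7 (SD 12.5, n = 618) and 12.5 (SD 12.2, n = 362); 50 patients per arm; attrition 33%.

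**Inputs assumed.** The protocol gives no completion rates by arm. EMDR completion is set at 67%, borrowed from the 33% attrition, which is a different quantity. TAU completion is set at 80%, 85% or 90%. The whole 3.8-day gap is first treated as prognostic. The true EMDR effect is set to zero.

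**The plan's own figures.**
- 12.5 − 8.7 = 3.8 days.
- Pooled SD = √[(617 × 12.5² + 361 × 12.2²)/978] = 12.39.
- d = 3.8/12.39 = 0.307 and f = d/2 = 0.153, matching the stated 0.31 and 0.15.
- The stated N of 74 reproduces with f = 0.15, three measurements and a within-patient correlation of 0.5 (power 0.806). The article does not state that correlation.

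**Model 1, normal selection.** A latent tendency to complete has correlation ρ with the reduction in heavy drinking days; p is the completion share and φ the normal density at its cut-off.
- Gap between completers and non-completers = ρ × φ/(p(1 − p)) × SD. At p = 0.67, φ = 0.362, so ρ = (3.8/12.39) × 0.67 × 0.33/0.362 = 0.187.
- Shift in the completers' mean = ρ × φ/p × SD: 1.25 days at 67%, 0.81 at 80%, 0.64 at 85%, 0.45 at 90%.
- Bias for EMDR = shift(67%) − shift(TAU share): 0.44, 0.62 and 0.80 days, or 12%, 16% and 21% of 3.8.
- If half the gap is prognostic: 6%, 8% and 11% of 3.8. If none is (pure dose): zero.
- Simulation with 50 per arm and no EMDR effect gave +0.45 (67/80) and +0.75 days (67/90) for the completers contrast. An instrumental-variable estimate gave −0.03 and −0.06.

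**Model 2, nested types.** Every patient who would complete EMDR would also complete TAU, and the additional TAU completers are 3.8 days worse. Bias = 3.8 × (1 − p_EMDR/p_TAU).
- 67/80: 3.8 × (1 − 0.67/0.80) = 0.62 days.
- 67/90: 3.8 × (1 − 0.67/0.90) = 0.97 days.
- More unequal completion gives more: 50/90 gives 3.8 × (1 − 0.50/0.90) = 1.69 days.

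**Equal completion.** With 67% in both arms and the same selection process, both models give zero.

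**Bias against precision.** Completers SE at 67/80 = 12.39 × √(1/33.5 + 1/40) = 2.90 days. With an SE of about 2.9, a bias of 0.44 to 0.80 raises the two-sided 5% error rate to about 5.3 to 5.9%. Simulation under Model 2 gave 5.7% (67/80) and 6.4% (67/90).

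**Precision of a complier estimate.** With non-adherence on one side only, it is the intention-to-treat effect divided by the completion share. Intention-to-treat SE = 12.39 × √(2/50) = 2.48; 2.48/0.67 = 3.7 days. Both SEs assume 50 randomised per arm with complete outcomes and no covariate adjustment.

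**The case against.** The primary inference is protected. Intention-to-treat is primary, the completers analysis is additional and is only said to give insight, and the Discussion's main goal is one that intention-to-treat answers. Pairing intention-to-treat with effectiveness and per-protocol with efficacy is a common convention, and the choice of estimator usually belongs in an analysis plan. Most of this stands and limits the weight of the point. It does not remove it, because the article itself states what the completers result means, and the design does not support that statement.

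Three stronger readings are tempting and are not supported:

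- *The protocol's own figures show that attendance is prognostic by 3.8 days.* They come from another study and contrast under 75% with over 110% of recommended attendance, leaving out the middle. Five of seven sessions is 71%, below that study's lower cut-off. The gap may be dose, selection or both, so it does not measure the bias.
- *The bias favours EMDR.* The EMDR section allows fewer sessions where fewer are required. Patients who needed four or fewer would be classed as premature terminators and leave the EMDR completers, which could work against EMDR. The TAU rule is also demanding, so higher completion in that arm is conjecture.
- *A spurious efficacy finding is likely.* Under the assumptions used, the error rate barely moves.

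The planned analyses of premature termination would help to show unequal completion, though they would not correct for it. It is also fair to say that a complier estimate is less precise (3.7 against 2.9 days) and is essentially intention-to-treat rescaled.

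**Conclusion.** The point holds as a misstatement about a secondary analysis. The Design and Analyses sections present a comparison of groups selected after randomisation, under arm-specific rules, as the answer to the efficacy part of the primary objective. The effectiveness conclusion is untouched.

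The possible bias runs from zero to roughly 0.4 to 0.8 days in favour of EMDR under the normal selection model, and up to about 1.0 under the nested model. Those figures rest on two assumptions: that the entire 3.8-day gap is prognostic, and that completion is 67% against 80 to 90%. Different completion shares change the size, and loss of patients who needed few sessions could reverse the sign. A reader should not infer that the trial's main result is compromised or that a particular bias has been shown. A change of wording and one additional model are justified.

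**What to change.** 1. In the Design and Analyses sections, describe the completers ANOVA as a supportive, non-randomised comparison, and remove the statement that it gives efficacy under ideal circumstances.

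2. For the efficacy question, add a complier average causal effect on change in heavy drinking days at one named time point. Include all randomised patients with the same multiple imputation as the intention-to-treat analysis. Use randomised arm as the instrument for EMDR received, and adjust for T0 heavy drinking days and randomisation stratum. The trial arranges no EMDR for the TAU-only arm (Randomization and allocation), so non-adherence to EMDR should be essentially one-sided.

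3. Report it for any EMDR session received and for five or more sessions. State that the five-session version assumes one to four sessions have no effect, and that both versions assume allocation acts only through the EMDR received.

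4. State that the estimate is essentially the intention-to-treat effect divided by the completion share, so it adds no independent test of effect.

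Cost: wording and one model on data already collected (arm, sessions attended, outcome). The interval is wider, with an SE of about 3.7 against 2.9 days at 50 per arm with complete data, and wider again with attrition.

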### Data collection

Subjects participate in the study for 8 months (from T0 to T3). Patients in both treatment conditions will be assessed identically (see Table 1). Two instruments are only used during the inclusion interview: the MINI-Plus [43] and the MATE 2.1 [44]. At T0, RA1 (blinded to treatment allocation) assesses baseline measurements of all primary, secondary, tertiary and quaternary variables. At T1 (post treatment), T2 (follow-up after 1 month) and T3 (follow-up after 6 months) all but one (the ‘readiness for change’ as measured with the RCQ-D [52] is only assessed at baseline) measurements are repeated by RA1.

For participants in the EMDR + TAU group additional assessments take place within (pre and post levels of distress, craving or positive affect of memory representations on a 11-pt Likert scale) and between (daily diary: number of drinks, intensity and frequency of craving, adverse events) sessions. These assessments are an integral part of the EMDR intervention manual and can therefore only be used to explore changes during the course of EMDR within this group. EMDR therapists also fill in a questionnaire after the last EMDR session of each participant regarding perceived and experienced treatment burden credibility and harm, before, during and after treatment.

RA1 also gathers demographic data: age, sex, social-economic and marital status, educational level, and ethnicity. Participant-report questionnaires (no 3–11 in Table 1 below [6,52-59]) will be provided digitally using Perseus web survey software [60]. The alcohol Timeline Followback interview (TLFB; [61]) is conducted face-to-face by RA1.

The alcohol Stroop [62] and valence IAT [63] will be administered using the program Inquisit 3 [64] for computerized assessment.

After each on-site assessment, participants are referred to a laboratory nearby for collection of blood samples to determine GGT and CDT [65]. Results are interpreted by an independent physician from IrisZorg. The results will be discussed with the participants after the last assessment by this physician, if relevant. In the case that lab results merit intervention before the last follow up assessment, the physician will notify the regular addiction care physician or general practitioner as soon as possible.

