##### Alcohol timeline followback (TLFB [60])

The Alcohol TLFB is a drinking assessment method that obtains estimates of daily drinking and has been evaluated with clinical and non-clinical populations. Using a calendar, people provide retrospective estimates of their daily drinking over a specified time period that can vary up to 12 months from the interview date. In this study retrospective estimates of the previous month will be used. Several memory aids can be used to enhance recall (e.g., calendar; key dates serve as anchors for reporting drinking; standard drink conversion). The Alcohol TLFB has been shown to have good psychometric characteristics with a variety of drinker groups, and can generate variables that provide a wide range of information about an individual’s drinking (e.g., pattern, variability, and magnitude of drinking). The method is recommended for use when relatively precise estimates of drinking are necessary, especially when a complete picture of drinking days (i.e., high- and low-risk days) is needed (evaluating drinking pre-posttreatment). Although Timeline summary data have been found to be generally reliable, as with all drinking assessment methods, exact day-by-day precision cannot be assumed or necessarily expected. Overall, the Alcohol TLFB method provides a relatively accurate portrayal of drinking, and has both clinical and research utility.

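### Time to first drink, a secondary outcome, is taken from a 30-day TLFB that misses 26 of 56 days before T1 and about 122 of 152 before T3, and is tested with an ANOVA that cannot handle censoring

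*Protocol article*

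**What the plan says.** The primary objective lists four operationalisations of drinking behaviour. The second is "time to first alcohol drink (only relevant if abstinence was reached before the previous assessment"). The same section then names change in heavy drinking days as the single primary outcome variable, and the Analyses section places time to first drink among the secondary variables.

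Four choices are fixed in the article itself:

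- **Visits** (Design): "post treatment (T1 = T0 + 8 weeks) and at follow up one (T2) and six months (T3) post treatment".
- **Recall window** (TLFB section): "In this study retrospective estimates of the previous month will be used". Table 1 gives the same window as 30 days.
- **Source** (Analyses): "time to first drink variable derived from TLFB data".
- **Test** (Analyses): "Repeated measures of continuous secondary variables such as time to first alcohol consumption" are to be analysed by repeated measures ANOVA, with two groups and, for this variable, three times (T1, T2, T3).

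The only survival method in the plan is a Kaplan–Meier estimate for premature treatment termination (PTT): the "survival curve will be used to illustrate the distribution of PTT prior to the completion threshold at session 5".

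**The concern.** The abstinence condition refers to the previous assessment, so the clock runs over the whole interval between two visits. The instrument looks back over only part of that interval at T1 and at T3. Someone who drinks in the unobserved part and then stops is recorded as not having drunk. Someone who drinks there and continues is given too late a date.

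Two analysis problems come on top of this. A participant who does not drink before the visit has no event time, only a lower bound, and an ANOVA on a continuous value has no place for that. And having a value at T2 or T3 depends on drinking after randomisation, which EMDR is meant to change, so the groups compared at those visits are no longer the randomised ones.

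At stake is the one planned outcome that times a return to drinking, in a trial whose Discussion puts relapse rates within its main goal.

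**Working it through.** **Plan's own figure.** The Data collection section says "Subjects participate in the study for 8 months (from T0 to T3"). With a month of 365.25/12 = 30.44 days, 56 days + 6 months = 7.84 months, which agrees. The visit intervals are therefore 8 weeks, 1 month and 5 months. The article gives no event count or power for time to first drink. Its sample size of 74 is for the primary outcome and does not bear on this point.

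**Coverage.** Unobserved days = interval length − 30.

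| Interval | Length (days) | Covered | Unobserved | Share unobserved |
|---|---|---|---|---|
| T0 to T1 | 56 | 30 | 26 | 26/56 = 46% |
| T1 to T2 | 30.4 | 30 | 0.4 | about 1% |
| T2 to T3 | 152.2 | 30 | 122.2 | 122.2/152.2 = 80% |
| T0 to T3 | 238.6 | 90 | 148.6 | 148.6/238.6 = 62% |

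**Can another instrument fill the gaps?** No. The daily diary is kept only in the EMDR arm during treatment, and the Data collection section limits it to exploration within that arm. The AUDIT is also set to one month and yields no dates.

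**How many first drinks fall in the gaps (illustration only).** The Background gives a one-year relapse above 85% across several addictions. Two assumptions are needed: that this figure stands in for any first drink, and that the hazard is constant. Then h = −ln(1 − 0.85)/365.25 = 0.00519 per day and S(t) = exp(−ht). The range shown is for one-year relapse of 50% to 95%.

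- T0 to T1: (1 − S(26))/(1 − S(56)) = 0.126/0.252 = 50% of first drinks fall in the gap (48% to 52%).
- T2 to T3: (1 − S(122.2))/(1 − S(152.2)) = 0.470/0.546 = 86% (82% to 89%).

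**Censoring, same assumptions.** Of those who enter an interval abstinent, the share with no drink by its end is S(56) = 75% at T1 (63% to 90%), S(30.4) = 85% at T2 (78% to 94%) and S(152.2) = 45% at T3 (29% to 75%). None of them has an event time.

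**Conditioning.** At T1 the condition concerns abstinence before T0, which precedes randomisation and does no harm. At T2 and T3 it concerns drinking during follow-up. If abstinence must be unbroken, a participant abstinent at T0 has the variable defined at all three times with probability S(56 + 30.4) = 64% (49% to 85%). A complete-case 2 × 3 ANOVA would keep only that subset, selected after randomisation.

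**The case against.** The strongest reply concerns reach. The article names one primary outcome, heavy drinking days in the past 30 days. It matches the TLFB window exactly, and neither it nor the sample size is touched. That stands, and it limits the severity.

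Other limits also stand:

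- A reader might infer that time to first drink cannot be observed at all. The T1 to T2 interval is covered, and so is just over half of T0 to T1. The loss is partial at T1 and severe at T3.
- A reader might infer that the whole comparison is non-randomised. Only T2 and T3 are affected.
- A reader might call this the only outcome that speaks to relapse. The article does not define relapse as any drink, prefers heavy drinking days because they reflect loss of control, and allows controlled drinking as a treatment goal.
- A reader might say that participants who never drink will be dropped or imputed. The article does not say how they are scored; they could be given the interval length, for example. But any such value puts a bound in place of an unknown time, so the objection to the ANOVA remains.

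What does not stand is leaving the point to a statistical analysis plan. The article itself fixes the window, the definition and the test, and they do not fit together.

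**Conclusion.** The concern holds for a secondary outcome. Followed as written, the plan misses or misdates first drinks in 26 of 56 days before T1 and about 122 of 152 days before T3, applies a method that cannot represent right-censored times, and compares subsets formed after randomisation at T2 and T3. The day counts rest only on the stated schedule, taken as kept, and the 30-day window. The shares of first drinks and of censored participants rest on the assumed constant hazard and relapse range, and show order of magnitude only.

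The documents do not support reading this as a threat to the primary result. It should be fixed, because otherwise the planned result for time to first drink cannot be interpreted.

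**What to change.** - **Data.** At T1 and T3, extend the TLFB look-back to the date of the previous assessment, 56 and about 152 days. The article says the method covers a "specified time period that can vary up to 12 months from the interview date". Keep the last 30 days as the window for the primary outcome.
- **Definition.** Use one time from randomisation to first drink, in participants abstinent at T0, censored at the last assessed date. This group is defined at baseline, so the comparison within it stays randomised. Starting the clock in all randomised participants would tell little, because the eligibility criteria admit people who still drink below the weekly limits.
- **Analysis.** Use Kaplan–Meier curves with a log-rank test or Cox model, and drop the ANOVA for this outcome. Six sites by up to three care pathways give up to 18 strata for 100 participants (100/18 = 5.6 each, fewer among the abstinent), so adjust for strata or pool them where sparse.
- **Visits already completed.** Recruitment and data collection have begun. Use interval-censored methods for visits done with the 30-day window, and treat the gap as unobserved rather than drink-free.

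Cost: a longer interview at two visits, less precise recall over about five months at T3 (the article itself warns that day-by-day precision cannot be assumed), and mixed ascertainment between earlier and later participants. The article does not say how many participants will be abstinent at T0, so the precision of this analysis is unknown. Those who become abstinent only after T0 will not contribute to it. No new instrument is needed.
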